## Abstract

**Background:**

Type 2 diabetes is a major public health problem in Australia with prevalence increasing in parallel with increasing obesity. Prevention is an essential component of strategies to reduce the diabetes burden. There is strong and consistent evidence from randomised controlled trials that type 2 diabetes can be prevented or delayed through lifestyle modification which improves diet, increases physical activity and achieves weight loss in at risk people. The current challenge is to translate this evidence into routine community settings, determine feasible and effective ways of delivering the intervention and providing on-going support to sustain successful behavioural changes.

**Methods/Design:**

The Sydney Diabetes Prevention Program (SDPP) is a translational study which will be conducted in 1,550 participants aged 50-65 years (including 100 indigenous people aged 18 years and older) at high risk of future development of diabetes. Participants will be identified through a screening and recruitment program delivered through primary care and will be offered a community-based lifestyle modification intervention. The intervention comprises an initial individual session and three group sessions based on behaviour change principles and focuses on five goals: 5% weight loss, 210 min/week physical activity (aerobic and strength training exercise), limit dietary fat and saturated fat to less than 30% and 10% of energy intake respectively, and at least 15 g/1000 kcal dietary fibre. This is followed by 3-monthly contact with participants to review progress and offer ongoing lifestyle advice for 12 months. The effectiveness and costs of the program on diabetes-related risk factors will be evaluated. Main outcomes include changes in weight, physical activity, and dietary changes (fat, saturated fat and fibre intake). Secondary outcomes include changes in waist circumference, fasting plasma glucose, blood pressure, lipids, quality of life, psychological well being, medication use and health service utilization.

**Discussion:**

This translational study will ascertain the reach, feasibility, effectiveness and cost-effectiveness of a lifestyle modification program delivered in a community setting through primary health care. If demonstrated to be effective, it will result in recommendations for policy change and practical methods for a wider community program for preventing or delaying the onset of type 2 diabetes in high risk people.

## Background

The number of people developing type 2 diabetes is rising dramatically worldwide with 439 million cases projected by 2030 [1]. This trend is mirrored in Australia where the prevalence of diabetes has more than doubled between 1981 and 2000 [2]. Currently in Australia there are over 1 million people with type 2 diabetes and approximately 8 per 1,000 people aged 25 years and older develop diabetes each year [3]. The annual health care costs in Australia of type 2 diabetes have been estimated at $2.2 billion AUD [4].

The increasing prevalence of diabetes, the increase in modifiable risk factors for the disease (obesity, sedentary behaviour and poor nutritional choices), as well as the severe and costly complications which can be difficult to prevent and treat, mean that prevention is an important strategy for reducing the burden of diabetes.

There is strong and consistent evidence from randomised controlled trials that type 2 diabetes can be prevented or delayed through lifestyle modification interventions which aim to improve diet, increase physical activity and reduce weight in people at high risk of developing the disease. The Finnish [5] and US [6] studies achieved a 58% reduction in diabetes incidence through lifestyle modification while the Chinese Da Qing study [7] achieved a 40% reduction in type 2 diabetes. Both the Finnish [8] and Chinese studies [9] showed long-term persistence of reduced diabetes risk over 7 and 20 years respectively. Similar benefits have been shown in the Japanese [10] and Indian [11] diabetes prevention trials, suggesting the generalisability of these findings.

Diabetes prevention programs recognise the importance of a theoretically-grounded behavioural intervention as a core component of the lifestyle modification, although no single behavioural theory has dominated. The behavioural programs have focused on encouraging physical activity and dietary changes and included various components such as initial assessment, individualised goal setting, individual counseling, on-going support, regular assessment and feedback and monitoring of behaviours and outcomes throughout the study.

Small community-based programs have reported some success in modifying surrogate markers for diabetes through lifestyle intervention. The Greater Green Triangle Diabetes Prevention Project in Australia [12] and the Good Ageing in Lahti Region Lifestyle Implementation Trial in Finland [13] confirmed that short-term lifestyle modification programs can reduce risk factors for diabetes in primary care settings.

The current challenge is to translate this evidence into cost-effective large scale community-wide programs. There is increasing acknowledgement that the best way to do this is through studies which have an explicit focus on generalisation and feasibility and which report information on contextual variables such as representativeness, reach, implementation and adaption, costs and other outcomes important to policy makers [14]. Thus the current study employs a design which will not only provide data on intervention effectiveness, but also will examine contextual factors through process evaluation central to what has been called by some the 'science of delivery' [15].

The overall aim of this study is to assess the effectiveness of a community-based lifestyle modification program on modifiable risk factors for type 2 diabetes. Additional aims include assessing the feasibility of delivering the program in a primary health care setting; identifying determinants of the interventions which are associated with and predict a beneficial outcome; and the costs and cost-effectiveness of the program.

## Methods/Design

The SDPP is a translational study based on the active arm of international randomised controlled trials demonstrating the effectiveness of lifestyle modification interventions in reducing the incidence or delaying the onset of type 2 diabetes in high risk individuals.

### Setting

Communities in three Divisions of General Practice, one in metropolitan Sydney, one in a semi-rural area and the other in a rural area of NSW, Australia.

### Ethics

Ethics approval to conduct this trial has been granted by the Research Ethics Review Committee of the Sydney South West Area Health Service - Eastern Zone (ID Number X08-0053). Written informed consent is obtained by all participants prior to enrolment.

### Participants and recruitment

The Divisions of General Practice have recruited over 75 practices and 150 general practitioners (GPs) to participate in the study. This was done through expression of interest by letter and fax, information sessions and site visits. The main pre-requisite for inclusion was the practice having a computerised patient record system.

People aged 50-65 years (18 years and older in the indigenous subgroup) without known diabetes attending study general practices are approached to participate. A variety of methods are used to identify potential participants including opportunistic recruitment when the person attends the general practitioner for a routine consultation, using the practice's computer database to identify people in the target age range and sending a letter suggesting they attend for risk assessment, and local media advertising of the program.

Risk is assessed using the AUSDRISK tool, a questionnaire developed in Australia [16]. The questions focus on demographic and diabetes risk factors and include an objective assessment of waist circumference performed by trained research staff. The maximum AUSDRISK score is 38 and a score of ≥ 15 is considered high risk. A score of 15-19 is associated with a 1 in 7 chance and a score of ≥ 20 with a 1 in 3 chance of developing diabetes over the next 5 years [16]. A score of ≥ 12 is considered high risk in the indigenous subgroup.

A person with a risk score of ≥ 15 is required to undergo investigations to exclude prevalent diabetes. This initially involves measurement of capillary blood glucose in the general practitioner's surgery, followed by measurement of fasting plasma glucose and possibly an oral glucose tolerance test.

Study exclusion criteria include new or previously diagnosed diabetes, taking a hypoglycaemic medication in the past month, use of prescribed weight loss medication or a medical contraindication to participation in a physical activity program. Participants enter the study after written consent is obtained, eligibility criteria have been met and clearance is received from their general practitioner.

The study plans to recruit 1,550 high risk people into the lifestyle intervention program. Among these 100 will be Arabic-speaking, 100 will be Chinese-speaking and 100 will be indigenous people.

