#### Impact Evaluation

Outcomes are assessed at baseline and 12 months by research staff, using a combination of in-person assessment and CATI questionnaires. Physical activity is assessed using the Physical Activity Scale for the Elderly (PASE), which has established reliability and validity [26]. Dietary intake (including total fat, saturated fat and fibre) is assessed by a self-completed 3-day non-weighed food record, which is analysed using Foodworks [27].

Weight, height, waist circumference and blood pressure are measured using standard methods. Blood is collected for measurement of fasting plasma glucose and lipids. Additional questions on socio-demographic characteristics, concomitant diseases and medications, smoking, alcohol, social support, self-efficacy for lifestyle change, and quality of life are asked at the baseline and 12 month CATI surveys.

Analyses of these data will determine whether the program goals are achieved by individuals, by the group as a whole and differentially by sub-groups (e.g. GP Division and gender). In addition, these data will be used to model the projected impact of the program beyond the 12-month intervention period.

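### The work-up to exclude prevalent diabetes is required from an AUSDRISK score of 15, but indigenous people count as high risk from 12, so scores of 12 to 14 are not covered as written

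*Protocol article*

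**What the plan says.** All the entry rules are in the protocol article under Participants and recruitment.

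- **General cut-off:** "a score of ≥ 15 is considered high risk", on a scale with a maximum of 38.
- **Subgroup cut-off:** "A score of ≥ 12 is considered high risk in the indigenous subgroup".
- **Testing rule, in the next paragraph:** "A person with a risk score of ≥ 15 is required to undergo investigations to exclude prevalent diabetes". The work-up is a capillary glucose in the practice, then a fasting plasma glucose, and possibly an oral glucose tolerance test.
- **Who is approached:** people "without known diabetes attending study general practices are approached to participate".
- **Exclusion:** "Study exclusion criteria include new or previously diagnosed diabetes", with no score attached.
- **Entry:** after written consent, once "eligibility criteria have been met and clearance is received from their general practitioner".

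The section plans 1,550 high-risk participants, 100 of them indigenous. Under Impact Evaluation, "Outcomes are assessed at baseline and 12 months by research staff", and "Blood is collected for measurement of fasting plasma glucose and lipids".

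**The concern.** The cut-off that makes someone recruitable and the cut-off that triggers diabetes testing should be the same number. They agree for the general population (15 and 15) but not for the indigenous subgroup (12 and 15).

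This matters because people are approached on the basis of having no *known* diabetes. Undiagnosed diabetes has to be looked for, and the glucose work-up is the only step the article describes for finding it before entry. Read literally, an indigenous person scoring 12 to 14 with undiagnosed diabetes could start a prevention program before the diagnosis is made. Two things are then at stake: correct application of the exclusion for new diabetes, and timely diagnosis for that person. A practice or later program following the published sentence would also test one group of high-risk people and not another.

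**Working it through.** The plan gives no figure to reproduce here. The check sets the stated thresholds side by side, looks for text elsewhere that closes the gap, and bounds the number of people concerned.

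**Step 1. Compare the score ranges.** All inputs are from Participants and recruitment.

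| Group | High risk | Work-up stated as required | High risk but not covered |
|---|---|---|---|
| General | 15 to 38 | 15 to 38 | none |
| Indigenous subgroup | 12 to 38 | 15 to 38 | 12, 13, 14 |

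The uncovered band is 15 − 12 = 3 score values.

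**Step 2. Look for another provision that requires testing at 12 to 14.**

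- *Exclusion of new diabetes.* It applies at every score, but it names a condition and not a test. It works only if someone looks for the condition.
- *General practitioner clearance.* It is required of everyone, but no glucose measurement is stated as part of it.
- *Baseline fasting plasma glucose.* It is described as an outcome measurement. No diagnostic limit, entry decision or action is attached to it.
- *Rest of the article.* No other text shown extends the work-up to scores of 12 to 14. Figure 1, the program overview, is not available in the text reviewed.

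**Step 3. Bound the number of participants.** The planned numbers are 1,550 in total and 100 indigenous. The article does not say how many of the 100 would score 12 to 14, so both extremes are shown.

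- Lower bound, if none score 12 to 14: 0 / 1,550 = 0%.
- Upper bound, if all do: 100 / 1,550 = 6.45%, or about 6.5%.
- Not affected under either extreme: 1,550 − 100 = 1,450, and 1,450 / 1,550 = 93.5%.

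**Step 4. Bound the extra testing among enrolled participants.** With one capillary and one fasting plasma glucose test each, the maximum is 100 + 100 = 200 tests and the minimum is 0. Oral glucose tolerance tests would be added for some. Their number cannot be derived, because the article makes that test conditional without giving a rate.

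**The case against.** The strongest reply is that the section, read as a whole, implies testing for everyone. New diabetes is excluded without a score limit, and it cannot be excluded unless it is sought. Entry also depends on the criteria being met and on the general practitioner's clearance, again at every score. On that reading, 15 is shorthand for the high-risk cut-off, whose subgroup variant was given just before. The testing sentence does not say that people below 15 are exempt, and nothing in the article shows that anyone was enrolled untested. A journal article also condenses the full protocol, which may set out the subgroup's pathway.

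Much of this stands. The text supports a mismatch in wording, not a finding that people with diabetes were admitted, and an oversight in drafting is the likelier explanation than a decision to leave the band untested. The safeguards keep the severity low.

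Two parts do not carry. First, the threshold is not a detail left out for brevity: the article states one, as a requirement, and it conflicts with the cut-off in the preceding paragraph. The same section does write out a subgroup variant for age (18 years and older instead of 50 to 65), so a reader would expect one here if it applied. Second, reaching universal testing from the exclusion criterion takes an inference that the explicit testing sentence does not support.

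**Conclusion.** The point holds as a minor inconsistency: the testing sentence is wrong as written for the indigenous subgroup. Scores of 12, 13 and 14 qualify as high risk without a stated diagnostic work-up before entry. Confidence is high for the mismatch itself. Whether any untested person was, or would be, enrolled cannot be judged from the article.

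The size rests on the planned recruitment numbers and on the unknown share of indigenous participants in the band, for which the full range from none to all was taken. Even at the upper end, the expected effect on whole-cohort results is negligible. The consequence is limited to eligibility and the protection of individual participants.

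**What to change.** In the testing sentence, replace the single threshold with both: a high-risk score, meaning ≥ 15, or ≥ 12 for indigenous people. The work-up itself stays as described.

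If anyone scoring 12 to 14 has already been enrolled without the work-up, review that person's baseline fasting plasma glucose and refer to the general practitioner if it is in the diabetic range.

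The cost is one phrase. If practices already test from 12, nothing else changes. If they do not, the added burden among enrolled participants is at most the 200 tests bounded above, plus tolerance tests in some. The study already uses all three tests.

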### Intervention - Lifestyle Modification Program

The five aims of the lifestyle modifications are:

1. At least 30 min/day of moderate to vigorous intensity physical activity, including aerobic exercise 3 or more days/week plus strength training at least twice/week (210 min/week total structured exercise)

2. Reduction in the intake of energy from total fat to less than 30%

3. Reduction in the intake of energy from saturated fat to less than 10%

4. Fibre intake of at least 15 g/1000 kcal

5. Achievement of a 5% reduction in body weight at 12 months.

In addition to the 210 min/week structured exercise goal, participants are encouraged to increase incidental physical activity in ways which would enhance both cardiovascular and musculoskeletal fitness.

These five goals are entirely concordant with the Finnish DPS (5), which was one of the most successful diabetes prevention trials. The physical activity goal, which has been modified slightly from the Finnish DPS is based on a review of the physical activity prescriptions utilised in relation to outcomes achieved in all of the successful trials of diabetes prevention (5,6,7,10,11), considerations of cost and feasibility in this translational setting, as well as other literature regarding modality, volume, and intensity of exercise required to improve metabolic risk and body composition in similar cohorts. Both the Finnish DPS and the US DPP included resistance training (strength training) in their supervised exercise sessions and is explicitly specified within the physical activity goal of the SDPP. Resistance training is an anabolic form of exercise, differing substantially from aerobic exercise in its ability to induce muscle hypertrophy and associated metabolic and functional changes [17,18]. It improves insulin sensitivity, glucose homeostasis, blood pressure, dyslipidaemia, markers of inflammation and catabolism, and visceral obesity, thus addressing the key metabolic abnormalities in adults at high risk of type 2 diabetes [19,20]. Importantly, resistance training (but not aerobic exercise) attenuates or prevents the loss of lean tissue (muscle and bone) accompanying weight loss diets such as those prescribed in this study [21].

The behavioural components are based on stages of change [22] and social cognitive theories [23]. The intervention is delivered by dedicated program lifestyle officers from a variety of health backgrounds including dietetics, nursing, psychology and exercise physiology. The lifestyle officers undergo specific training in health coaching, group program delivery and standardized data collection used for evaluation. The health coaching approach incorporates principles from self-management, removing psychological blocks to change and confidence [24].

An overview of the program and the evaluation plan is shown in Figure 1.

**Figure 1 F1:**
[figure not shown]
**Overview of the program and data collection points for evaluation**.

High risk individuals agreeing to participate in the lifestyle modification program complete an initial computer-assisted telephone interview (CATI) survey. This survey includes socio-economic and demographic information, physical activity habits, quality of life, and self-efficacy, as well as recent health service utilisation and current medication use. Participants are then scheduled to attend an individual consultation with a lifestyle officer. At this consultation, the lifestyle officers measure height, weight and waist circumference using calibrated stadiometers, scales and tape measures, following a standardized anthropometric protocol as specified by the International Society for the Advancement of Kinanthropometry (ISAK) [25]. The individual consultation includes a general discussion about diabetes risk and prevention, an overview of the program, and uses motivational interviewing techniques to assist participants to set goals and develop tools to self-monitor. Following this session, arrangements are made for participants to attend three two-hour group programs held over a six to eight week period. Lifestyle officers conduct these group sessions of approximately 10 people, which cover theoretical, behavioural and practical aspects of diet and physical activity. The overall program motto is: "Eat better and move more". Those who are not able to or do not want to attend a group program are offered the option of three individual health coaching sessions by telephone, covering the same material. The intervention delivered to indigenous participants will be slightly modified to take account of cultural issues.

Follow up telephone calls are made by the lifestyle officers to each participant at 3, 6 and 9 months to enquire about progress, assist with behaviour change and offer participants additional support as required.

In addition, participants are provided with details of local community-based lifestyle programs which have been evaluated by the research staff and found to be consistent with the goals of the SDPP. Participants have the option of enrolling in such programs as one way to assist in achieving the SDPP physical activity and dietary goals.

At 12 months the CATI survey is repeated and participants undergo an individual assessment with the lifestyle officer and their general practitioner.

### Outcome measures and evaluation plan

The evaluation plan has three components:

1. Impact evaluation measures changes at 12 months in the key outcomes known to be associated with reduced diabetes incidence: weight loss; increase in moderate to vigorous physical activity (including both aerobic and strengthening activities); increase in dietary fibre consumption; decrease in fat consumption and decrease in saturated fat intake. Program and participant factors which predict these outcomes are assessed.

2. Process evaluation measures program reach, fidelity, satisfaction and knowledge of program delivery by staff, satisfaction of consumers, and identifies facilitators and barriers associated with program implementation and delivery.

3. Economic evaluation involves health system and individual perspectives and estimates implementation costs, costs per outcome and cost-effectiveness.

#### Impact Evaluation

Outcomes are assessed at baseline and 12 months by research staff, using a combination of in-person assessment and CATI questionnaires. Physical activity is assessed using the Physical Activity Scale for the Elderly (PASE), which has established reliability and validity [26]. Dietary intake (including total fat, saturated fat and fibre) is assessed by a self-completed 3-day non-weighed food record, which is analysed using Foodworks [27].

Weight, height, waist circumference and blood pressure are measured using standard methods. Blood is collected for measurement of fasting plasma glucose and lipids. Additional questions on socio-demographic characteristics, concomitant diseases and medications, smoking, alcohol, social support, self-efficacy for lifestyle change, and quality of life are asked at the baseline and 12 month CATI surveys.

Analyses of these data will determine whether the program goals are achieved by individuals, by the group as a whole and differentially by sub-groups (e.g. GP Division and gender). In addition, these data will be used to model the projected impact of the program beyond the 12-month intervention period.

